### Statistical methods

Descriptive statistics will be used to summarise information collected on each group statistics. Statistical significance will be assumed at *p* < 0.05.

#### Primary analysis method

A repeated measures generalised linear model will be used to compare the mean number of frailty criteria between randomisation groups over time. The effect of potential confounders (age, number of co-morbidities, number of prescribed medication, cardiovascular health status, energy intake) will be adjusted for in the regression models.

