A fall will be defined as “an unexpected event in which the participant comes to rest on the ground, floor, or lower level”, as per guidelines published by the Prevention of Falls Network Europe (ProFaNE) [36]. In ascertaining falls at baseline, participants will be asked “In the previous 12 months, have you had any fall including a slip or trip in which you lost your balance and landed on the floor or ground or lower level?” Falls will be recorded prospectively by the participant using a fall calendar where the participant marks daily if they had a fall. The monthly fall calendar will be returned to the University of Auckland in provided prepaid postage envelopes. Telephone interview by an interviewer blinded to group allocation will be carried out to ascertain further details of falls and injuries, and to follow-up with participants if the monthly fall calendar is not received or to rectify missing data. A blinded medically trained assessor will examine all fall reports to ensure a defined fall has occurred and establish the presence of injury. Injury will be categorised as absent if none recorded, mild to moderate for report of pain, inability to perform usual activities after the fall, bruising, and contusions. Severe injury is any fracture (excluding finger fracture) or any admission to hospital overnight. Rate of falls, risk of falls, and time to first fall will be reported as recommended by Lamb et al. [36].

The validated short physical performance battery (SPPB) will assess physical performance [37]. The SPPB is an objective assessment tool for evaluating lower extremity functioning in older persons. It consists of three parts: the Balance Test, the Gait Speed Test, and the Chair Stand Test, and it can be administered in approximately 10 min. It has a score between 0 and 12 points, the higher the score the better the physical performance. The SPPB is a widely used measure of physical performance for it is practical and safe to be administered by trained assessors in home setting [38].

Functional status will be assessed using the Nottingham Extended Activities of Daily Living (NEADL), a commonly used instrument for assessing activities of daily living within four categories: mobility, kitchen activities, domestic activities and leisure activities. It has a score between 0 and 22, the higher the score the better the functional status [39, 40].

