### Allocation

The randomisation sequence will be prepared by an independent statistician using computer-generated block randomisation and uploaded to the Electronic Data Capture (EDC) system by an administrator of the EDC. The randomisation sequence was stratified by study sites (Whangarei, Howick-Auckland, Tauranga, Invercargill) and ethnic groups (Māori/Pasifika and non-Māori/Pasifika). The allocation sequence will be concealed to all study investigators and the study coordinators involved in enrolment. Local study coordinators will assign the intervention group through the EDC after the assessors complete baseline assessments. Once randomisation has occurred, the study coordinators and participants are not blinded to group allocation. The study coordinators systematically remind all participants not to disclose the group allocation to the assessors prior to the follow-up appointments.

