#### Secondary analysis methods

Fall data will be summarised as number of falls, number of fallers/non-fallers/frequent fallers, fall rate per person year, and time to first fall.

The absolute risk difference between groups will be reported. We will use negative binomial regression to estimate the difference in fall rates between groups. The effect of potential confounders (number of co-morbidities, number of prescribed medication, use of psychotropic medications and cardiovascular health status) will be adjusted for in the regression models. Interactions between falls and frailty (overall and separately for gender and ethnicity) will be examined.

For outcomes with baseline and the post-intervention 24-month follow-up measures only, comparisons of continuous variables between groups will be performed using *t* tests. Where the continuous variables are not normally distributed, non-parametric comparisons using the Wilcoxon rank-sum test will be used. Categorical measures will be compared using the Chi-square test. For outcomes with repeated measures (more than two measurements), generalised estimating equations (GEE) will be used with clustering on participant and an exchangeable correlation matrix.

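### The covariate lists for the frailty and falls models leave out the two stratification factors and the baseline value of each outcome, a modest and avoidable loss of precision

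*Protocol article*

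**What the plan says.** - **Strata.** The Allocation section reports: "The randomisation sequence was stratified by study sites (Whangarei, Howick-Auckland, Tauranga, Invercargill) and ethnic groups (Māori/Pasifika and non-Māori/Pasifika". That is 4 × 2 = 8 strata.
- **Primary model.** The section on the primary analysis method states: "A repeated measures generalised linear model will be used to compare the mean number of frailty criteria between randomisation groups over time". It then lists five adjustment variables: "The effect of potential confounders (age, number of co-morbidities, number of prescribed medication, cardiovascular health status, energy intake) will be adjusted for". Site, ethnic group and the baseline number of frailty criteria are not among them.
- **Falls model.** The section on secondary analysis methods specifies negative binomial regression with its own list: "The effect of potential confounders (number of co-morbidities, number of prescribed medication, use of psychotropic medications and cardiovascular health status) will be adjusted for". Site, ethnic group, age and previous falls are not among them.
- **Ethnicity elsewhere in the analysis.** It appears once: "Interactions between falls and frailty (overall and separately for gender and ethnicity) will be examined". That is an exploratory interaction, not an adjustment of the treatment effect.
- **What is collected before randomisation.** The Blinding section has all primary and secondary outcomes measured before allocation. Under Outcome measures, fall history is asked at baseline: "In the previous 12 months, have you had any fall".
- **Outcome and analysis set.** The primary outcome is defined as change in frailty score. The section on data collection, management and analysis keeps every randomised participant with a baseline measurement in the intention-to-treat analysis, including those lost to follow-up.

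**The concern.** Stratified blocks make the arms alike within each site and ethnic group. A model that leaves the strata out still counts the variation between them as random error, so its standard errors do not match the design. Ethnic group may well be prognostic here, because Māori and Pasifika participants enter from age 60 and others from age 75.

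The baseline value of an outcome is often its strongest single predictor. Both lists name other predictors and leave this one out: the frailty score in one model, previous falls in the other. At stake is precision in the primary comparison and in the main secondary one, using data that the trial already holds.

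**Working it through.** **Inputs from the article.** There are 126 participants per group, 90% power, a two-sided 5% level and a difference of 0.43 criteria (Sample size section). The article gives no SD, no correlation between baseline and follow-up scores, and no share of variance due to site or ethnic group. The last two are therefore assumed over ranges below.

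**The plan's own figure.** Without an SD, 126 per group can only be inverted. For a pairwise comparison, SD = 0.43 × √(126/2) / (1.960 + 1.282) = 1.053. For the factorial margins of 252 v 252 the same inversion gives 1.489. The figure can be neither confirmed nor refuted, and the two calculations below do not use it.

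**1. Omitting the strata.** Let R² be the share of residual variance, after the named covariates, that site and ethnic group explain.

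- Overstatement of the standard error = 1/√(1 − R²) − 1
- True two-sided alpha = 2 × [1 − Φ(1.960/√(1 − R²))]

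| Assumed R² | SE too large by | True alpha |
|---|---|---|
| 0.01 | 0.5% | 0.049 |
| 0.05 | 2.6% | 0.044 |
| 0.10 | 5.4% | 0.039 |

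These values are for a linear model. The direction carries over to the falls model; its size was not derived.

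**2. Omitting the baseline frailty score.** Let r be the correlation between baseline and follow-up scores, with equal variances. For a contrast at one follow-up visit, the variance relative to an analysis of follow-up alone is:

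- baseline ignored: 1
- change contrast, with baseline as an unconstrained response: 2(1 − r)
- baseline as a covariate: 1 − r²
- baseline as a response with a common mean across arms: essentially 1 − r²

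Covariate adjustment against a change contrast is (1 − r²)/[2(1 − r)] = (1 + r)/2.

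| Assumed r | Change contrast | Covariate | Covariate ÷ change | Gain over change | Gain over ignoring baseline |
|---|---|---|---|---|---|
| 0.4 | 1.20 | 0.84 | 0.70 | 30% | 16% |
| 0.5 | 1.00 | 0.75 | 0.75 | 25% | 25% |
| 0.6 | 0.80 | 0.64 | 0.80 | 20% | 36% |

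Against a model with a common baseline mean, the gain is essentially nil.

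**3. Omitting fall history.** The article gives nothing from which to size this. As an illustration only, if previous falls cut the variance of the log rate ratio by an assumed 3% to 10%, the standard error is multiplied by √0.97 = 0.985 to √0.90 = 0.949.

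**The case against.** **The lists may not be exhaustive, and a separate analysis plan may settle this.** The variables are labelled as potential confounders, and the Covariates section mentions falls among the data collected. But that section describes data collection and puts nothing into a model. The article also spells out a list for each of two models. The point therefore concerns what it fixes, although a fuller plan may already extend the lists.

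**Baseline may already be in the primary model.** This stands in large part. A change outcome, a repeated-measures comparison over time, and an analysis set that keeps people with only a baseline measurement all fit a model with baseline as a response. A reader might infer that the baseline information is discarded and that chance imbalance goes uncorrected. The article does not support either inference: a change contrast subtracts the baseline. What can remain is inefficiency.

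**A large power gain is not established.** A reader might take the SD of 1.053 and the 120 per arm left after 20% attrition (600 × 0.8 / 4), and conclude that adjustment lifts power from 88.6% to between 93.2% (r = 0.4) and 97.7% (r = 0.6). That assumes baseline is otherwise ignored and that the design is powered on pairs of arms, although the article describes a 2 × 2 factorial. It also assumes that the undisclosed SD is not already that of an adjusted or change analysis.

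**Age covers part of the ethnicity link.** This is true in the primary model, where age is listed. It is not true in the falls model, which omits age. Any ethnic difference beyond age is plausible but not shown in the article.

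**Conclusion.** The omissions are real and worth correcting, but the loss is one of precision.

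- **Strata:** no bias, and tests slightly conservative. The standard error is overstated by 0.5% to 5.4% and true alpha is 0.049 to 0.039, for an assumed R² of 0.01 to 0.10. Calling the p-values invalid would overstate this.
- **Baseline frailty:** the loss is undetermined because the role of baseline is not stated. It ranges from essentially nothing (common baseline mean), through 20% to 30% of the variance (change contrast, r 0.6 to 0.4), to 16% to 36% (baseline ignored, r 0.4 to 0.6).
- **Fall history:** its omission from the negative binomial model gives up precision of unknown size.

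The textual facts are firm. Every figure rests on assumed correlations or variance shares.

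**What to change.** 1. Add site and ethnic group as fixed effects to the primary frailty model and to the negative binomial falls model.
2. In the primary model, state how the baseline frailty score is used. It can be a covariate, or a response in a repeated-measures model with baseline means constrained equal across arms. The second form keeps participants who have only a baseline measurement, as the intention-to-treat paragraph requires. The covariate form, with only follow-up scores as the response, would drop them.
3. Add prior-year falls to the negative binomial model. No change is proposed for time to first fall, because the article lists it as a summary and names no model for it.

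**Cost.** No new data are needed. The strata add four parameters to each model (three for site, one for ethnic group), and the baseline score or prior-year falls adds about one more. The wording should be settled before unblinded outcome data are seen, so that the choice of covariates cannot be read as post hoc.

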**Methods:**

A multi-centre randomised controlled assessor-blinded study. The four intervention groups are SC, an 8-week nutrition education and cooking class; SAYGO, a 10-week strength and balance exercise class; SC plus SAYGO, and a social group (Control). Community-dwelling adults aged 75+ (60 + Māori and Pasifika) in New Zealand are recruited through health providers. Participants are not terminally ill or with advanced dementia, and have a score of 1 or 2 on the FRAIL questionnaire. Baseline assessments are completed using standardised questionnaires prior to randomisation. Four follow-up assessments are completed: immediately after intervention, 6, 12 and 24 months post-intervention. The primary outcome is frailty score, secondary outcomes are falls, physical function, quality of life, food intake, physical activity, and sustainability of the strategy. Study outcomes will be analysed using intention-to-treat approach. Cost analyses will be completed to determine if interventions are cost effective relative to the control group.

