## Background

Frailty is a precursor to functional loss [1]. It is a multidimensional geriatric syndrome involving several inter-related physiological systems described as a reduction in reserve to meet homeostatic challenge, meaning frail older people are vulnerable to poor outcomes [2] including increased risk of falls, impaired cognitive function, worsening disability, hospitalisation, residential care admissions and mortality [3]. Up to 17% of community-dwelling older people aged 65 + have been reported as frail with 42% pre-frail [3, 4]. In octogenarians, over 60% have been reported to be pre-frail [5].

In the pre-frail state, an older person has homeostatic mechanisms to respond to external stressors, but less than those who are not frail. This transition phase may provide a window of opportunity to prevent deterioration of health outcomes and to maintain quality of life.

Several strategies have attempted to reduce frailty to improve outcomes, with physical activity and nutrition being the most commonly tested interventions [6]; however, results are inconsistent and a greater focus on prevention is needed to reduce the poor outcomes associated with frailty.

Older people are vulnerable to poor nutritional status [7] and inadequate food intake is related to pre-frailty and frailty [8]. Supplements increase weight, particularly in those with malnutrition [9] but the impact of supplements on frailty is uncertain and their wider implementation may be costly. In the InCHIANTI study, 700 + older people, mean age 73 years, adherence to a healthier dietary pattern was associated with a lower risk of being frail over 6-year follow-up [10]. Self-preparation of meals stimulates appetite and is associated with intake of more nutritious meals [11]. Cooking also involves physical and social skills (e.g. shopping for ingredients) and cognitive abilities [11]. Senior Chef (SC) is a programme developed in New Zealand to increase knowledge and practical skills in shopping, cooking and general nutrition for older people. The programme has been evaluated [12] but impact on health outcomes is uncertain.

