Health-related quality of life will be assessed with the Short Form (SF-12) including the summary scores for physical and mental health-related QOL [41]. Individual-level responses from the SF-12 can be translated into a preference-based quality of life measuring health on a utility scale where ‘dead’ scores 0 and ‘full health’ scores 1. These repeated individual utilities can be used to construct QALYS [41] by plotting time against quality of life and identifying the area under the plotted curve. This QALY measure identifies health over a period of time and is used in the cost-effectiveness analysis.

Process outcomes will also be used as secondary outcomes, namely food intake and reduced sedentary time. Food intake will be assessed using the INTAKE24, an online dietary tool developed by a team in Newcastle University, Newcastle upon Tyne, UK [42]. INTAKE24 is based on the 24-h multiple-pass recalls (MPR) dietary assessment with the New Zealand FOODfiles 2016 database incorporated into the programme. The MPR protocol is suitable for use in the general [43] and oldest old population and matches that used in the Newcastle 85+ and LiLACS NZ studies [44, 45]. Two 24-h MPR will be completed on two separate days (a weekday and a weekend) by a trained interviewer at the participants’ residence or a venue suitable for them.

Physical activity will be determined using the CHAMPS Activities Questionnaire. CHAMPS is a validated questionnaire to measure sedentary (1 METs), low-light (> 1 and ≤ 2 METs), high-light (> 2 and < 3 METs), moderate-to-vigorous physical activity (MVPA, ≥ 3 METs), and total activity in older people over a 4-week period [34, 35].

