### Data collection, management, and analysis

Data will be collected with face-to-face interviews and physical assessments using a standardised questionnaire completed by trained research assessors blinded to the group status of the participant in the participant’s home or local clinic. Data will be entered directly to the EDC system. Assessors are trained over a 2-day training period for all measures including standardisation. Assessors will meet regularly to support each other and observe each other’s procedures. Research-trained assessors blinded to group status will complete covariate and outcome assessments at baseline, end of the intervention (0 month  post-intervention), 6 months, 12 months and 24 months post-intervention.

Data entered in the EDC will be verified for completeness by the data quality assurance research team (see “Monitoring” section). Data from the EDC will be transferred to a statistical package (SAS and SPSS) for analysis. INTAKE 24 data are automatically linked to NZ FOODfiles and macro- and micronutrients are calculated.

The primary approach for analysis of primary and secondary outcomes will follow the intention-to-treat principle, for all participants who have at least one baseline measurement. All randomised participants will be analysed in the group they were allocated to, even if they do not attend the allocated intervention programme, are lost to follow-up, or die thereby preserving the intention-to-treat framework. The primary approach for analyses will be supplemented by a secondary analysis which will be a per-protocol analysis of outcomes for those who participated in the interventions and includes only observed cases (i.e. participants with measurements at baseline to the 24 months).

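### The primary model adjusts for energy intake without limiting it to baseline, although food intake is a trial outcome on the path from the nutrition programme to frailty

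*Protocol article*

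**What the plan says.** Under Primary analysis method the protocol article specifies the model: "A repeated measures generalised linear model will be used to compare the mean number of frailty criteria between randomisation groups over time". It then states that "potential confounders (age, number of co-morbidities, number of prescribed medication, cardiovascular health status, energy intake) will be adjusted for in the regression models". No time of measurement is attached to any of the five covariates.

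Elsewhere the article treats intake as an outcome. The abstract states that "secondary outcomes are falls, physical function, quality of life, food intake, physical activity, and sustainability of the strategy". The Outcome measures section adds: "Process outcomes will also be used as secondary outcomes, namely food intake and reduced sedentary time". Table 1 places INTAKE24 in its block of outcome measures, at baseline and at 0, 6, 12 and 24 months. Energy is derived from that instrument: "INTAKE 24 data are automatically linked to NZ FOODfiles and macro- and micronutrients are calculated". The Covariates section does not list energy or food intake.

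On timing, the data collection section says that assessors "will complete covariate and outcome assessments at baseline, end of the intervention" and at the later visits. Table 1 shows medical history and medications at baseline, 12 and 24 months.

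**The concern.** In a randomised comparison a baseline covariate is adjusted for to gain precision. A variable measured after randomisation that the treatment is meant to change is a different matter: it is a mediator, and conditioning on it takes out of the group effect whatever passes through it.

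The article's own rationale puts intake in that position. The Background says "Self-preparation of meals stimulates appetite and is associated with intake of more nutritious meals", links inadequate intake to pre-frailty and frailty, and ties energy intake to the maintenance of weight. Weight loss is one of the five criteria counted in the primary outcome. The Discussion presents the process outcomes as changes that come before clinical improvement.

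At stake is the meaning of the primary estimate in the two arms that receive Senior Chef. The article promises an intention-to-treat analysis. With follow-up energy intake in the model, the Senior Chef coefficient would instead be an effect at fixed energy intake. It could also be biased if unmeasured health influences both intake and frailty, because conditioning on intake then opens a path that randomisation had closed.

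**Working it through.** **Reading the sections together.** Energy intake is in the primary model (Primary analysis method); its source is an outcome instrument used at every assessment (Table 1); it is absent from the Covariates list; and it lies on the hypothesised path to frailty (Background, Discussion). No sentence restricts the model to baseline intake, and none says that follow-up intake will be used. Both models fit the text.

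**The plan's own figure.** Inputs from Sample size: 126 per group, difference 0.43 (1.68 to 1.25), 90% power, two-sided 5%. No standard deviation is printed, so I solve for it:

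SD = 0.43 / [(1.960 + 1.282) × √(2/126)] = 1.053

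In the other direction, SD 1.05 gives n = 126 per group. The stated sample size is therefore consistent with an SD of about 1.05, but it cannot be reproduced independently.

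**Illustration.** Let f be the share of the Senior Chef effect that runs through energy intake. The article gives no value, so f is assumed. If adjustment removes that share, the remaining effect is 0.43 × (1 − f), and

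power = Φ(effect / SE − 1.960), with SE = 1.053 × √(2/n).

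SE is 0.1327 for n = 126 (two single arms) and 0.0938 for n = 252 (Senior Chef yes v no, pooling over SAYGO). For f = 20% and n = 126: 0.344 / 0.1327 = 2.59, and Φ(2.59 − 1.96) = Φ(0.63) = 74%.

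| Assumed share f | Remaining effect | Power, 126 v 126 | Power, 252 v 252 |
|---|---|---|---|
| 0 | 0.43 | 90% | 99.6% |
| 20% | 0.344 | 74% | 96% |
| 30% | 0.301 | 62% | 89% |
| 50% | 0.215 | 37% | 63% |

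**Check by simulation.** I used a linear model with one follow-up, 126 per group and 3,000 runs. Assumptions: the programme shifts intake by 0.4 SD, baseline and follow-up intake correlate at 0.5, and there is no unmeasured common cause. With f = 50% the estimated reduction was 0.433 without adjustment, 0.434 with baseline intake and 0.220 with follow-up intake; power was 90%, 92% and 47%. With f = 25% the reductions were 0.427, 0.427 and 0.320; power was 89%, 90% and 68%. Baseline adjustment leaves the effect intact and follow-up adjustment removes the mediated share. Power at f = 50% is 47% here rather than 37% because the covariate also reduces the residual variance, which the formula ignores.

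**The case against.** The strongest reply is that the harmful model is nowhere stated. A reader might infer that the plan puts follow-up intake into the primary model, since the model is a repeated-measures one and covariates are assessed at several visits. The document does not support that: repeated-measures models routinely take fixed baseline covariates, and a condensed article may leave their timing to the full plan. The schedule even favours baseline values for some covariates. Medical history and medications are not collected at 0 or 6 months, so a concurrent value is missing at two of the four follow-ups.

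This stands as far as it goes, and it makes the point conditional. It does not remove the point. INTAKE24 has a value at every assessment, so the gap in the schedule does not protect the one covariate that matters most. Nor is this mere omission: the article itself selects the variable, calls it a confounder and assigns it to the primary model, while treating it elsewhere as an outcome.

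A second reply concerns size, and it also stands. The shares are assumed. Energy is narrower than food intake, and Senior Chef also teaches menu planning, budgeting and shopping. Two 24-hour recalls measure intake with noise, so adjustment would remove less than the full mediated share. The factorial margins lose less power than single-arm comparisons.

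Third, the falls model does not include energy intake. The mediation argument therefore does not carry over to it; only the question of covariate timing does.

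**Conclusion.** The point holds in conditional form. The text permits a primary analysis in which the Senior Chef estimate, alone or combined with SAYGO, is not the intention-to-treat effect. That happens only if post-randomisation energy intake enters the model; baseline intake is harmless.

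Two stronger conclusions are tempting and not supported. One is that the trial's primary estimate will be a direct effect: the article does not say which values are used. The other is that the bias must run towards no effect: removal of a beneficial mediated part does, but unmeasured health affecting both intake and frailty could push the estimate either way.

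The size cannot be derived from the document, which gives no effect of the programme on energy intake. The tabulated power losses rest on the assumed shares, full removal of the mediated part, the implied SD of 1.053 held constant and, at the margins, a Senior Chef effect that is the same with and without SAYGO. They show that the choice could matter, not how much it will.

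**What to change.** In Primary analysis method, state that every adjustment covariate is a pre-randomisation value. For energy intake, either specify the baseline INTAKE24 value or drop it from the model. If the role of follow-up intake is of interest, analyse it in a separate analysis labelled as mediation, apart from the primary estimate.

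Use the same baseline-only wording for co-morbidities, prescribed medications and cardiovascular status in the primary model, and for the covariates of the falls model under Secondary analysis methods, because medical history and medications are collected again at 12 and 24 months. It would also help to replace the term confounder with baseline covariate.

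The cost is a sentence or two in the analysis section. No new data are needed and the sample size is unaffected. The wording should be settled before unblinded data are seen, so that nobody later chooses between two models that estimate different things.
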